#### Individual Dietitian Assessment and Advice

All participants will receive a personalized nutrition assessment and dietary advice aligned with principles of healthy eating for reducing cardiometabolic risk [28]. These principles are informed by evidence-based dietary patterns, including Mediterranean-style and DASH (dietary approaches to stop hypertension) diets [28], and focus on eating fruit, vegetables, whole grain cereals, healthy protein sources (especially fish, legumes, nuts, and seeds), unflavored dairy foods, healthy fats and oils (including extra virgin olive oil), and the use of herbs and spices instead of salt. This advice will be provided by an accredited practicing dietitian (APD) in an in-person appointment. The advice will be tailored to personal preferences and goals.

#### Wearable Activity Monitor

All participants will be provided with a Fitbit Inspire HR (Fitbit, Inc) device and its accompanying mobile app to monitor physical activity. The heart rate reserve (HRR) method will be used to quantify moderate-to vigorous-intensity physical activity (40-89% HRR), with resting heart rate measured at baseline and maximal heart rate estimated as follows: 208 – (0.7 × age) [46]. For participants taking beta-blocker medication, which affects heart rate, a more representative equation will be used: 168 – (0.51 × age) [47]. At the baseline assessment, participants will be instructed on how to use the Fitbit, including how to download the app and synchronize the device, and will be provided with an information booklet. Each participant will have a Fitbit account established with a study-specific email address that will be accessible to study staff. This will permit appropriate real-time data extraction for the study. If no device data is present for 7 days during the study period, participants will be contacted via text or phone call to troubleshoot. Participants will keep the device after the end-of-program assessments.

### Intervention

Participants randomized to the intervention group will be offered access to a suite of health technology options with both core (text message support) and optional (electronic dietary education resources, group-based exercise physiology and dietetics videoconferencing appointments, and an unsupervised online or mobile app home exercise program) components. Exposure to the frequency of text messages and the number and type of optional components will be patient-led, with participants choosing their preferred level of engagement (Figure 1). Participants will choose their components after randomization and the research project officer will confirm their choice via phone call in week 1. The core and optional components are described in the following sections.

#### Text Message Support

All intervention participants will receive lifestyle-related text messages. The text messages will be semipersonalized and unidirectional (Table 3). They will reflect selected behavior change techniques to help facilitate change in dietary and physical activity patterns [48,49]. Participants will be able to select the desired frequency of text messages: once, twice, or three times per week for the duration of the intervention.

**Table 3 table3:** Text messages and relation to behavior change technique constructs.

Behavior change technique constructs	Text message examples
Social support	“Telling your helpful family and friends about your goals will help you achieve them”
Prompt specific goal setting	“2 serves of fruit every day is an important goal”
Behavior substitution	“Swapping 2 red meat meals for fish is a great way to get healthy sources of protein and fats!”
Prompt self-monitoring of behavior	“Monitor your resistance and aerobic exercise training sessions using the Fitbit watch and app”
Provide information about behavior-health link	“Resistance exercise twice a week increases muscle size and strength, helping you lose weight and keep healthy”
Problem solving	“Are you finding it hard to get 30 minutes of physical activity every day? Start with a smaller amount and build from there. Every little bit helps!”
Provide instruction	“To get more fiber from fruit, keep the skin on and aim for 2 serves per day”

#### Option 1: Electronic Dietary Education Resources

Participants can choose to have access to online and mobile app–based nutrition information from Sophus (Sophus Health Pty Ltd). These include nutrition fact sheets, nutrition information videos, personal journals, and recipes promoting the principles of healthy eating for reducing cardiometabolic risk [28].

#### Option 2: Group Based Videoconferencing Appointments (Dietetics)

Participants can choose to have access to group dietitian telehealth sessions (maximum 6 participants per group) via the Queensland Health telehealth portal. Sessions will be run by an APD and will be offered monthly. Sessions will last for 45 minutes and focus on principles of healthy eating for reducing cardiometabolic risk.

#### Option 3: Group Based Videoconferencing Appointments (Exercise Physiology)

Participants can choose to have access to group exercise telehealth sessions (maximum 6 participants per group) via the Queensland Health telehealth portal. Sessions will be run by an accredited exercise physiologist (AEP) and will be offered weekly. Sessions will last for 60 minutes. Participants will also be offered a personalized home exercise program prescribed through Physitrack (Physitrack Ltd, London, UK).

#### Option 4: Unsupervised Online and Mobile App Home Exercise Program

Participants can choose to access an unsupervised personalized home exercise program prescribed through Physitrack. This option does not include exercise telehealth sessions with an AEP. Home programs will be individually updated monthly by an AEP.

#### Exercise Intervention

Further details for the exercise intervention can be seen in Multimedia Appendix 2. In brief, participants opting into one of the two exercise options will be asked to achieve a minimum of 150 minutes of moderate- to vigorous-intensity aerobic exercise, and complete two 30-minute resistance exercise sessions per week. Participants who choose either exercise option will be provided with equipment (resistance bands with light and medium resistance grades) to facilitate resistance exercise. The prescribed videoconferencing exercise sessions will consist of 20 minutes of aerobic exercise, 30 minutes of resistance exercise, and 5-minute warm ups and cool downs. The AEP will remind the participants of their target heart rate zone and ask them to monitor their heart rate during the training session with their wearable activity monitor. The repetitions in reserve (RiR) method will be utilized for prescribing resistance exercise intensity via autoregulation [50]. Autoregulation allows resistance training to be adjusted in response to an individual’s performance in the session [51]. The prescribed exercise sessions will include 2 to 4 sets of a load between 1 to 4 RiR utilizing the provided equipment or body weight exercises. Participants who choose either exercise option will be provided with a personalized home exercise program following the same plan as the videoconferencing sessions.

### Statistical Analysis

#### Sample Size

As this will be a feasibility study, a sample size calculation was not performed for the primary outcome. To allow for reliable findings, the sample size calculation was conducted using the MetSSS for clinical effectiveness as a secondary outcome. Assuming a correlation of 0.5 between baseline and 26-week MetSSS and an effect size of 0.42 (representing a change of 0.8 in the intervention group and no change in the control group, with a pooled standard deviation of 1.9), the Stata procedure “sampsi” suggests that 67 participants per arm will be required to achieve 80% power to detect a significant difference at the 5% level (2-sided) using an analysis of covariance (ANCOVA). Allowing for 20% dropout, the required number of participants to be recruited will be 168 (84 per arm).

#### Primary Analysis

The primary analysis will evaluate the feasibility of the intervention. As mentioned previously, the feasibility of the intervention will be determined by evaluating safety and if three of the following four criteria are achieved: (1) recruitment rate ≥50%, (2) retention ≥70%, (3) exposure uptake ≥75%, and (4) telehealth adherence ≥80%. Safety will be assessed by comparing the number of study-related SAEs in the intervention and control groups using a chi-square test of homogeneity. The safety of the intervention will be assumed if there are no statistical differences between the groups.

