**Methods:**

The study is a single-center, 26-week, randomized controlled trial. The setting is specialist kidney and liver disease clinics at a large Australian tertiary hospital. The participants will be adults with a complex chronic condition who are referred for dietetic assessment and display at least one feature of the metabolic syndrome. All participants will receive an individualized assessment and advice on diet quality from a dietitian, a wearable activity monitor, and standard care. Participants randomized to the intervention group will receive access to a suite of health technologies from which to choose, including common base components (text messages) and optional components (online and mobile app–based nutrition information, an online home exercise program, and group-based videoconferencing). Exposure to the optional aspects of the intervention will be patient-led, with participants choosing their preferred level of engagement. The primary outcome will be the feasibility of delivering the program, determined by safety, recruitment rate, retention, exposure uptake, and telehealth adherence. Secondary outcomes will be clinical effectiveness, patient-led goal attainment, treatment fidelity, exposure demand, and participant perceptions. Primary outcome data will be assessed descriptively and secondary outcomes will be assessed using an analysis of covariance. This study will provide evidence on the feasibility of the intervention in a tertiary setting for patients with complex chronic disease exhibiting features of the metabolic syndrome.

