### Primary Outcome

The primary outcome is feasibility (Table 2), which will be used to inform future service delivery. Feasibility success will be confirmed if the intervention is safe (defined as a similar number of study-related serious adverse events [SAEs] between groups) and if three of the following four criteria are fulfilled: (1) ≥50% of all referred eligible patients are recruited (recruitment), (2) ≥70% of intervention participants undergo an end-of-program assessment (retention), (3) ≥75% of intervention participants have a higher frequency of specialist outpatient dietetic and exercise specialist contact than the controls (exposure uptake), and (4) videoconferencing-facilitated dietetic and exercise sessions have an attendance rate of ≥80% of the total scheduled contacts (telehealth adherence).

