#### Safety

Safety will be determined from adverse event reporting. SAE categories and adverse events of special interest are detailed in Textbox 2. SAEs will be classified by event category, the outcome of the event, the relationship to the study, and by whether they were planned or unplanned. The relationship of the SAE to the study will be determined by medical review. All adverse events will be monitored and recorded via the REDCap research management system throughout the study [29]. In addition, all participants will be asked by a member of the research staff at the end-of-program assessment whether any unreported SAE or adverse event had occurred during the study period.

List of serious adverse events and adverse events of special interest to be recorded and monitored during the study period.

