#### Secondary Analyses

Analysis for continuous clinical outcomes will be conducted via an ANCOVA to compare change values between study groups, adjusted for baseline values and patient population (ie, patients with chronic kidney disease, hepatology, and kidney and liver posttransplant). No imputation of missing values will occur.

Supplementary descriptive analysis of participant technology choices and patient-led goal attainment will be conducted. Summative statistics for the proportion of engagement among participants in the intervention arm will be collected and analyzed postintervention. A significance level of *P*<.05 will be used for all analyses.

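### Safety, a required condition for feasibility success, is concluded from a non-significant chi-square test, with no acceptable excess or confidence bound stated

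*Protocol article*

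**What the plan says.** Under Primary Outcome, safety is the one criterion that cannot be traded against the others: "Feasibility success will be confirmed if the intervention is safe" and at least three of four further criteria (recruitment, retention, exposure uptake, telehealth adherence) are met. Safe is there "defined as a similar number of study-related serious adverse events [SAEs] between groups"; how close is close enough is not stated.

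Under Primary Analysis this becomes a test and a decision rule: "Safety will be assessed by comparing the number of study-related SAEs in the intervention and control groups using a chi-square test of homogeneity". The next sentence reads "The safety of the intervention will be assumed if there are no statistical differences between the groups". The threshold is given under Secondary Analyses: "A significance level of *P*<.05 will be used for all analyses".

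The Sample Size section says that no calculation was made for the primary outcome. The 168 participants (84 per arm) come from the metabolic syndrome severity score, a secondary outcome. No expected rate of study-related SAEs is given. The abstract says "Primary outcome data will be assessed descriptively".

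**The concern.** A test of homogeneity takes equality as its null hypothesis. A non-significant result says only that the data did not contradict equality; with few events almost no data would. The rule therefore treats absence of evidence as evidence of safety. Its incentive is also perverse: the fewer the participants or the less complete the reporting of events, the more likely the safe verdict.

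This matters because the verdict is a condition of the primary conclusion, which is meant to guide service delivery. A report could state that the intervention was shown to be safe when the data were compatible with a sizeable excess of related SAEs.

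**Working it through.** **Inputs from the article.** 84 per arm, 1:1 allocation; chi-square test on two groups; threshold P<.05; study-related SAEs as the endpoint.

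**Assumptions.** Participants with at least one event are counted, and all 84 per arm are analysed. Control-arm risk is taken from 1% to 10%, since the article states none.

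**The plan's own sample size.** Difference 0.8, SD 1.9, correlation 0.5, 80% power, two-sided 5%: n = 2(1.96 + 0.8416)² × 1.9²(1 − 0.5²) / 0.8² = 66.4, so 67 per arm. Dividing by 0.8 for dropout gives 83.75, so 84 per arm. The figure reproduces, but it says nothing about the safety test.

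**Which splits pass as safe.** With n = 84 per arm, a and b participants with events in the intervention and control arms, and t = a + b, the uncorrected statistic is X² = 168(a − b)² / [t(168 − t)]. It is significant above 3.841.

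| Split (a v b) | X² | P | Verdict under the rule |
|---|---|---|---|
| 3 v 0 | 168×9/(3×165) = 3.055 | .081 | safe |
| 6 v 1 | 168×25/(7×161) = 3.727 | .054 | safe |
| 8 v 2 | 168×36/(10×158) = 3.828 | .0504 | safe |
| 4 v 0 | 168×16/(4×164) = 4.098 | .043 | not safe |

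At 6 v 1 the Newcombe 95% confidence interval for the risk difference runs from −0.5 to +13.6 percentage points. The rule would call that result safe.

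With 0, 1, 2 or 3 control participants affected, the intervention arm needs at least 4, 7, 9 or 10 for significance. With Fisher's exact test it needs 6, 8, 10 or 11.

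**How often a true excess passes as safe.** For each pair of true risks, the binomial probabilities of all tables with P ≥ .05 were summed.

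| True risk, intervention v control | Ratio | Called safe, uncorrected chi-square | Called safe, Fisher |
|---|---|---|---|
| 3% v 1% | 3 | 89% | 98% |
| 5% v 1% | 5 | 69% | 87% |
| 6% v 2% | 3 | 77% | 88% |
| 8% v 2% | 4 | 59% | 72% |
| 9% v 3% | 3 | 65% | 75% |
| 10% v 5% | 2 | 78% | 85% |
| 10% v 2% | 5 | 40% | 53% |
| 15% v 5% | 3 | 40% | 49% |
| 20% v 5% | 4 | 13% | 18% |
| 30% v 10% | 3 | 8% | 12% |

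With 67 per arm the test is weaker still: 6% v 2% would be called safe about 80% of the time (power 0.199). For scale only, 80% power at two-sided 5% would need about 376 per arm for 6% v 2%.

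**The case against.** The best defence is that this is a feasibility study the article describes as low-risk, never sized for safety, with relatedness of SAEs judged by medical review. The rule is also not blind: 4 v 0 would already fail it with the uncorrected test. All of that is true. But a feasibility design explains low power; it does not justify drawing a positive conclusion from low power. Medical review, as described under Safety, decides whether an SAE is related to the study; it does not replace the decision rule.

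Other points a reader might infer are not supported, or carry little weight:

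- *That a several-fold excess would usually be certified as safe.* No SAE rate is stated, and at higher rates or larger ratios this fails: 15% v 5% and 10% v 2% pass only about 40% of the time, and 20% v 5% passes 13%.
- *That the test wrongly counts recurrent events, or is invalid with small expected counts.* The wording may be shorthand for participants with an event. The counting unit and small-cell handling are details an article commonly leaves to the full protocol or analysis plan.
- *That leaving falls, musculoskeletal injury and chest pain outside the criterion is an error.* The article records them as adverse events of special interest, and such an event counts if it also meets an SAE category and is judged study-related. Restricting the criterion to related SAEs is a stated choice; adding these events or all-cause SAEs is a preference.
- *That a significant benefit would fail the condition.* Literally so, because the test has no direction, but this would need at least 4 v 0 against the control arm and has little practical weight.
- *That the abstract flatly contradicts the analysis section.* The abstract compresses five components into one sentence, and only safety is tested. This is a matter of aligning wording.

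**Conclusion.** The point stands for the decision rule. As written, non-significance is taken to establish safety, safety is mandatory for the primary conclusion, and nothing defines how large an excess would be unacceptable. That flaw does not depend on any assumed event rate.

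Its practical size does. At assumed control risks of 1% to 3%, a true three-fold excess passes as safe in about 65% to 89% of trials with the uncorrected test. At control risks of 5% and 10%, a three-fold excess passes in about 40% and 8%. The low end is the more plausible one, given the low-risk description, the restriction to study-related events and 26 weeks of follow-up, but the article gives no figure to confirm this. The calculations assume that participants are counted and that 84 per arm are analysed.

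**What to change.** - Delete the sentence that assumes safety from the absence of a statistical difference.
- Report participants with at least one study-related SAE by arm with exact 95% confidence intervals, and the risk difference with a 95% confidence interval.
- Base the safety verdict on whether the upper limit for excess harm in the intervention arm stays below a value the sponsor fixes in advance, read together with the medical review. Replace the unquantified similarity wording under Primary Outcome with the same definition.
- If a P value is kept, use Fisher's exact test, as supportive only.
- Minor: align the abstract's description of the primary analysis with the Primary Analysis section.

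The cost is a change of wording and a few tables from data already collected. The downside is that, with few events, the verdict may have to be imprecise where the present rule would have said safe. How wide the interval will be at 84 per arm should be considered when the acceptable excess is set.

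### Safety, the one feasibility condition that cannot be missed, is inferred from a non-significant chi-square test with no margin or interval, in a trial not sized for that test

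*Protocol article*

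**What the plan says.** The Primary Outcome section makes safety a precondition: "Feasibility success will be confirmed if the intervention is safe (defined as a similar number of study-related serious adverse events [SAEs] between groups", with three of four further criteria (recruitment, retention, exposure uptake, telehealth adherence) also to be met. One of those four may fail; safety may not.

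The Primary Analysis section turns this into a rule. Safety is assessed by "comparing the number of study-related SAEs in the intervention and control groups using a chi-square test of homogeneity", and then "The safety of the intervention will be assumed if there are no statistical differences between the groups". The Secondary Analyses section sets the 5% significance level for all analyses. No acceptable excess, confidence interval or expected SAE rate is given.

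On size, the Sample Size section states that "a sample size calculation was not performed for the primary outcome"; the 168 participants come from the Metabolic Syndrome Severity Score (MetSSS), a secondary outcome. The Abstract (Methods) says "Primary outcome data will be assessed descriptively". The Safety section adds that medical review will determine each SAE's relationship to the study, that adverse events are recorded throughout, and that participants are asked about unreported events at the end.

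**The concern.** A non-significant test shows only that the data do not exclude equality. It does not show that the arms are alike, and without a margin or interval nothing says how large an excess remains possible. The rule also rewards imprecision: for a given true excess, fewer participants or fewer events make a safe verdict more likely.

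Few events are a reasonable expectation here, because only study-related SAEs count and the Recruitment section calls the study low-risk. The safety verdict gates the overall feasibility conclusion, which the Primary Outcome section says will inform future service delivery. A required part of the trial's main conclusion would therefore rest on a test that may have little ability to fail.

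**Working it through.** **1. The plan's own figure.** Inputs from Sample Size: difference 0.8, SD 1.9, correlation 0.5, two-sided 5%, 80% power, 20% dropout.

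n per arm = 2(1.960 + 0.842)² × 1.9² × (1 − 0.5²) / 0.8² = 66.4, so 67. Then 67 / 0.8 = 83.75, so 84 per arm and 168 in total. The stated figure reproduces, but it concerns MetSSS only.

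**2. Assumptions for the safety test.** The outcome is taken as participants with at least one study-related SAE, with 84 per arm and two-sided P<.05. Event rates are assumed, because the article gives none.

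**3. Observed splits (intervention vs control).** With equal arms of n, and a and b participants with events, uncorrected Pearson is X² = 2n(a − b)² / [(a + b)(2n − a − b)].

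- 3 vs 0: 168 × 9 / (3 × 165) = 3.05, P=.081, passes as safe.
- 6 vs 1: 168 × 25 / (7 × 161) = 3.73, P=.054, passes as safe. Observed excess 5/84 = 6.0 points; Newcombe 95% CI −0.5 to 13.6.
- 8 vs 2: 168 × 36 / (10 × 158) = 3.83, P=.0504, passes as safe.
- 4 vs 0: 168 × 16 / (4 × 164) = 4.10, P=.043, fails. Fisher's exact test gives P=.12 and the continuity-corrected chi-square P=.13, so either would pass it.
- 0 vs 0: the formula is 0/0 and undefined.

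At 4 vs 0 the expected number with events is 2 per arm, and at 6 vs 1 it is 3.5, so the chi-square approximation is doubtful there.

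**4. Probability of a safe verdict.** Power is the sum of the binomial probabilities of all tables with P<.05; a safe verdict has probability 1 − power (uncorrected Pearson).

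| Control vs intervention | Power | Declared safe |
|---|---|---|
| 1% vs 3% | 11.1% | 88.9% |
| 2% vs 6% | 23.5% | 76.5% |
| 3% vs 9% | 35.2% | 64.8% |
| 5% vs 10% | 22.2% | 77.8% |
| 1% vs 5% | 31.3% | 68.7% |
| 5% vs 15% | 59.7% | 40.3% |
| 1% vs 10% | 77.7% | 22.3% |
| 0% vs 10% | 97.4% | 2.6% |

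The first three rows are a tripled risk at control rates of 1–3%, declared safe in about 65–89% of trials. With the continuity correction power falls further: 1.9% for 1% vs 3% and 12.1% for 2% vs 6%. For scale, 80% power would need about 769 per arm at 1% vs 3% and 376 at 2% vs 6%.

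**5. What zero events would show.** The Wilson upper limit for 0/84 is z²/(n + z²) = 3.84 / 87.84 = 4.4%. The Newcombe upper limit for the difference at 0 vs 0 is therefore also 4.4 points.

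**The case against.** Several points on the other side are sound.

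- **Large excesses.** A reader might infer that an unsafe program would usually be called safe, or that any tripling of risk would be missed. The figures do not support that. Power is 78% at 1% vs 10% and 97% at 0% vs 10%; a tripling from 5% to 15% is detected in 60% of trials (47% with the continuity correction). The result belongs to low event rates, and those are assumed. At 1% vs 3% the expected counts are 0.84 and 2.52 participants; whether that excess makes a program unsafe is a clinical judgement.
- **Contradiction.** A reader might infer that Primary Analysis contradicts Primary Outcome. It does not. One section asks for similar counts without defining the term; the other says how that will be judged. The operational rule is weak, but the two are compatible. Calling 6 vs 1 dissimilar would apply a threshold the article never sets.
- **The abstract.** Its statement on descriptive assessment summarises five components, four of which are proportions set against thresholds. It does not override the methods text. The wording merits aligning, no more.
- **Feasibility trials are not sized for safety.** True, and openly stated. That is a reason not to draw a safety conclusion from a null test; it does not justify the rule.
- **Other safeguards.** Medical review, continuous recording and the end-of-program enquiry mean that the P value is not the only safety information. They do not alter the rule that decides the verdict.
- **Left to the analysis plan.** The choice of small-sample test could be. The decision rule could not: the article fixes it.

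**Conclusion.** The point stands in a limited form. The article infers a mandatory condition of its primary conclusion from non-significance, without a margin or interval, in a trial not sized for the comparison. That flaw does not depend on any assumed rate.

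Its size does. With 84 per arm, participants as the unit and control rates of 1–3%, a tripled risk passes as safe in about 65–89% of trials under uncorrected Pearson, and splits such as 3 vs 0 and 6 vs 1 pass. Large absolute excesses would usually be caught. At low counts the verdict can also change with the test variant, as 4 vs 0 shows.

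**What to change.** - In Primary Analysis, remove the sentence that assumes safety from the absence of a statistical difference, and stop using the chi-square test as the deciding step.
- Report study-related SAEs by arm, with the risk difference (participants with at least one event) and its 95% CI by Newcombe or an exact method.
- Base the safety judgement on that descriptive comparison together with the medical review already described under Safety, and state the largest excess that the interval does not exclude.
- Align the wording of the Abstract, Primary Outcome and Primary Analysis.

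A prespecified margin is optional and is for the investigators to set. They should know that 0 vs 0 already leaves an excess of up to 4.4 points unexcluded, so any smaller margin would fail even with no events.

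The cost is wording and one interval, with no extra participants or data. The safety claim becomes more modest. Because the article reports that enrollment has commenced, this changes a primary success criterion during the trial and should be dated, justified and documented.
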